**Table 1 Tab1:**
[figure not shown]
The schedule of enrolment, interventions, and assessments

*BJSQ* Brief Job Stress Questionnaire, *EQ-5D-5L* the Japanese five-level version of the scale by the EuroQoL group, *UWES* Utrecht Work Engagement Scale, *iOSDMH* Implementation Outcome Scales for Digital Mental Health, *K6* Kessler Psychological Distress Scale, *WHOHPQ* World Health Organization Health and Work Performance Questionnaire

#### Depression and anxiety

Depression and anxiety (non-specific psychological distress) will be measured using the Japanese version of the K6 scale [43]. It comprises six items that assess the frequency of experience of non-specific psychological distress, which are rated on a five-point Likert scale (0 = none of the times and 4 = all the times). The reliability and validity of the Japanese version of the K6 have been confirmed previously [43]. In this study, the total score for the K6 scale will be considered an indicator of depression and anxiety.

#### Psychosocial factors at work

Job stressors, stress responses, and psychological safety will be measured as indicators of psychosocial factors at work. Job stressors include job demands, job control, and social support from supervisors and coworkers, which will be measured using subscales of the Brief Job Stress Questionnaire (BJSQ) [48]. The BJSQ was developed in 2000 in Japan and has been widely used in occupational health studies and practice [49]. The subscales for job stressors comprise three items each and are job demands, job control, supervisor support, and coworker support. All items are rated on a four-point Likert scale (for job demands and job control: 1 = not at all, 4 = very much so; for supervisor and coworker support: 1 = not at all, 4 = extremely). The total subscale scores will be calculated.

Stress responses will also be measured using the BJSQ, and the subscales are vigor (three items), anger-irritability (three items), fatigue (three items), anxiety (three items), depression (six items), and physical complaints (11 items). All items are rated on a four-point Likert scale (1 = almost never, 4 = almost always). The total subscale scores will be calculated.

Psychological safety will be measured using the Japanese version of the Psychological Safety Scale (also known as PSS) [50]. It assesses workers’ perceptions of the consequences of interpersonal risks in the workplace and consists of three subscales: team leader (nine items, e.g., “If I had a question or was unsure of something in relation to my role at work, I could ask my team leader”), peers (seven items, e.g., “I can communicate my opinions about work issues with my peers”), and team as a whole (three items, e.g., “It is easy to ask other members of this team for help”) [51]. All items are rated on a seven-point Likert scale (1 = strongly disagree, 7 = strongly agree). The total subscale scores will be calculated.

#### Work engagement

The nine-item Japanese version of the Utrecht Work Engagement Scale (also known as UWES) will be used to assess work engagement [52]. It consists of three subscales, namely vigor (three items, e.g., “At my job, I feel strong and vigorous”), dedication (three items, e.g., “I am enthusiastic about my job”), and absorption (three items, e.g., “I am immersed in my work”). All items are rated on a seven-point Likert scale (0 = never, 6 = always). The reliability and unidimensional validity of the Japanese version of this scale have been confirmed previously [52]. The average scores from each of the nine items will be used for analyses.

#### Health-related QOL

Health-related QOL will be measured using the Japanese five-level version of the scale by the EuroQoL group (also known as EQ-5D-5L) [53]. It consists of five dimensions of QOL (mobility, self-care, usual activities, pain or discomfort, and anxiety or depression). Each dimension has five levels for perceived problems, and a higher score indicates a higher QOL. We will use the value set of the Japanese version of this scale that has been developed in previous research [54].

#### Subjective well-being

Job and life satisfaction will be measured as indicators of subjective well-being using questions from the BJSQ [48, 49], with one item for each: “I am satisfied with my job” and “I am satisfied with my family life,” respectively. The two items are rated on a four-point Likert scale (1 = dissatisfied, 4 = satisfied), with higher scores indicating higher satisfaction.

The Japanese version of the Workplace PERMA Profiler will also be used as a multidimensional concept of well-being [55]. This scale is based on Seligman’s PERMA model, and consists of five domains: positive emotion (P), engagement (E), relationships (R), meaning (M), and accomplishment (A) [56]. An overall score of well-being at work is calculated as the average of 15 items (three items each for five dimensions) and happiness (one item). All items are rated on an 11-point Likert-type scale (ranging from 0–10; e.g., for the first item of positive emotion, 0 = never and 10 = always). The reliability and validity of the Japanese Workplace PERMA Profiler have been confirmed previously [55].

#### Economic outcomes

Economic outcomes include work performance, absenteeism, worksite turnover, and monthly salary and yearly bonuses. Work performance will be assessed using an item for the absolute score of work performance from the Japanese version of the World Health Organization Health and Work Performance Questionnaire short version (also known as WHOHPQ) [57]. The item rates an individual’s overall job performance in the past month on a scale of 0‒10 (0 = worst job performance, 10 = best job performance). The ratings are multiplied by 10 to calculate work performance according to the scoring guidelines.

Regarding absenteeism, data on absent days in the year before the surveys, monthly salary, and yearly bonus will be obtained from the worksite database at the time of the baseline survey and the 12-month follow-up survey. Regarding worksite turnover, data on the employees leaving the worksite will be obtained at the 12-month follow-up survey.

#### Physiological outcomes from a health checkup

Data on physiological outcomes, based on the annual health checkups conducted by the participating worksites, will also be collected at baseline and at the 12-month follow-up surveys. These outcomes include height, weight, waist circumference, blood pressure, blood lipids, and blood glucose levels.

#### Cortisol extracted from fingernails

In total, 800 employees will be asked to clip extended fingernails into a zip-lock plastic bag for one month, and cortisol levels will be measured from the nail samples. This procedure will be conducted at baseline and at the 6- and 18-month follow-ups. During sample collection, health conditions and lifestyle topics associated with cortisol levels and fingernails will be assessed using a self-reported questionnaire. The questionnaire will include items on marital status, educational background, income, medical history, current medications, pregnancy/childbirth in the previous year, smoking and drinking habits, frequency of cutting nails, frequency of using manicures, how to shorten nails (cut only or cut and file), habit of biting nails, frequency of soap use, frequency of hand disinfection, and frequency of kitchen detergent use.

#### Process and implementation outcomes

For process evaluation, the completion rates of the intervention and active control programs will be collected from the digital records of the programs. Implementation outcomes will be assessed using the Implementation Outcome Scales for Digital Mental Health (also known as iOSDMH), which was shown to have acceptable reliability and validity [58]. This assessment tool was developed to measure the implementation outcomes of mental health interventions delivered by digital and telecommunication technologies, and comprises the following five subscales: acceptability (three items), appropriateness (four items), feasibility (six items), overall satisfaction (single item), and harm (five items). These evaluations will be conducted immediately after each intervention.

### Sample size calculation

The required sample size has been calculated according to the guidelines of the Consolidated Standards of Reporting Trials (also known as CONSORT) for cRCTs [59], considering the intraclass correlations of the outcomes nested by the worksites. The sample sizes in cRCTs should be multiplied by the design effect (1 + [m-1]ρ), where m is the average cluster size and ρ is the intraclass correlations [60]. In the dataset from a cohort of healthy Japanese workers [61, 62], the intraclass correlation for depression and anxiety measured by the K6 scale was 0.013. Therefore, a very small intraclass correlation (0.05, 5% of the outcome would be shared at the worksite level) was estimated for the primary outcome in this study. The average cluster size (the number of employees within one worksite) was set to 130 based on the information about potentially recruiting 2,700 companies from IID Co. Ltd.

The effect size of the four intervention programs on the primary outcome, that is, depression and anxiety, was estimated to be 0.20 in the standardized mean difference (d). A previous RCT that offered an Internet-based cognitive behavioral approach to prevent depression among nonclinical workers reported the effect size (d) of the intervention as 0.20 at the 6-month follow-up [63]. The effect sizes of work environment improvement and physical activity promotion on mental health among nonclinical workers were reported to be larger [35, 64]. An alpha error probability (α) has been set to 0.05/4 = 0.0125 (one-tail) because we plan four tests between the intervention programs and control programs. The statistical power (1-β) has been set to 0.80.

Based on these parameters, the required sample size has been calculated as 3,554 for each arm using G* Power version 3.1.9.2 [65]. Considering that the average number of employees within one worksite is assumed to be 130, 27.3 worksites will be needed in each arm. Therefore, we have set the required number of worksites and employees to 28 and 3,640 in each arm and to 140 and 18,200 in total.

The required number of worksites (140) is 5.2% of the recruited companies (2,700). Previous RCTs on nonclinical workers at multiple worksites in Japan reported acceptance rates of approximately 4% [63, 66]. In this cRCT, the acceptance rate is likely to be higher and to reach the target sample size by prioritizing the recruitment of stressful worksites, which may in turn require countermeasures for stress management.

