### Statistical analysis

For the main analysis, repeated-measures multi-level mixed modeling will be used to test the effects of each intervention compared with the control at the 6-, 12-, and 18-month follow-ups. The interaction effect of the group (1 = intervention, 0 = control) by time will be considered an indicator of the intervention effect. The multi-level is based on employees (level 1) and worksites (level 2). The variables used in the stratified randomization (i.e., worksite size, industries, and the percentage of “high-stress” employees in the worksites) will be used as covariates. Intention-to-treat analysis will be adopted by including all employees who completed the baseline survey in the analysis. Multiple imputations will be conducted for missing values owing to dropouts. Effect sizes will be calculated as the standardized mean differences (d) of the scores on the K6 scale, based on the estimated mean differences.

The primary endpoint of the primary outcomes is set at the 6-month follow-up, and the corresponding statistical significance will be the primary indicator of effectiveness. If recruitment does not achieve the target sample size (140 worksites and 18,200 employees in total), we will assess the intervention effectiveness based on a minimally important difference. As the estimated effect size of the interventions is 0.20, the distribution-based approach [67] is useful for estimating the minimally important difference of depression and anxiety measured by the K6 scale. In a previous RCT among nonclinical workers in Japan [63], the standard deviation of the change in the K6 score at the 6-month follow-up was 4.16. From the distribution, 20% of the standard deviation is estimated to be 0.832. Therefore, a 0.85 score change in the K6 score at the 6-month follow-up is considered to be the minimally important difference.

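### The equal 0.05/4 split over the four primary contrasts is valid, but Holm at the same family-wise 0.05 would give more power with no added recruitment

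*Protocol article*

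**What the plan says.** The article's Sample size calculation sets the level: "An alpha error probability (α) has been set to 0.05/4 = 0.0125 (one-tail"). The reason it gives is "because we plan four tests between the intervention programs and control programs". The other inputs are in the same section:

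- Power: "The statistical power (1-β) has been set to 0.80".
- Effect size for the four programmes together: "was estimated to be 0.20 in the standardized mean difference (d").
- Intraclass correlation: "a very small intraclass correlation (0.05, 5% of the outcome would be shared at the worksite level").
- Cluster size: "The average cluster size (the number of employees within one worksite) was set to 130".
- Inflation: the individual-level size is "multiplied by the design effect (1 + [m-1]ρ), where m is the average cluster size and ρ is the intraclass correlations".

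The result is 3,554 employees per arm, rounded up to 28 worksites and 3,640 employees per arm.

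The Statistical analysis section compares each intervention with control and places the primary endpoint at 6 months. It adds that "the corresponding statistical significance will be the primary indicator of effectiveness". It names no other level. The one-tailed 0.0125 is the only alpha in the document, and the primary hypothesis under Objectives is directional.

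**The concern.** An equal Bonferroni split holds every contrast to 0.0125 however the other three turn out. That is the best a plain split can do if only one programme works. The plan instead expects all four to work, with d = 0.20 each. Once one null hypothesis has been rejected, fewer remain that could be falsely rejected, and a stepwise procedure can relax the threshold for the rest. A fixed split forgoes this.

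What is at stake is the chance that an effective programme is declared effective, in a trial of 140 worksites that cannot easily be repeated. The sidedness also matters for the power statement, because the 80% was computed for one-tailed tests and does not carry over to two-sided ones.

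**Working it through.** **1. Reproduce the plan's figure.** All inputs are from Sample size calculation.

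- Design effect = 1 + (130 − 1) × 0.05 = 7.45.
- Individual-level n per arm for d = 0.20, one-tailed 0.0125, power 0.80, two-sample t-test with noncentral t: 477. The normal approximation, 2 × (2.241 + 0.842)² / 0.20², gives 476.
- 477 × 7.45 = 3,553.65, i.e. 3,554 per arm, and 3,554 / 130 = 27.3 worksites. This matches the article.
- Two-sided 0.0125 would give 560 × 7.45 = 4,172, and two-sided 0.05 would give 394 × 7.45 = 2,935. Neither matches, so the one-tailed 0.0125 was indeed used.

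**2. Power and error at the planned size.**

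- Effective n per arm = 3,640 / 7.45 = 488.6.
- Standard error of d = √(2 / 488.6) = 0.06398, so the expected z = 0.20 / 0.06398 = 3.126.
- One-tailed 0.0125 (critical value 2.241): power = Φ(3.126 − 2.241) = 0.81.
- Family-wise error, one-sided: at most 4 × 0.0125 = 5.0%. It is 4.9% if the tests were independent, and about 4.1% with the correlation of 0.5 that a shared control and equal arms imply.

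Both of the plan's own targets are met.

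**3. Replace the equal split by Holm at one-sided family-wise 0.05.** Order the four p-values and compare the smallest with 0.05/4 = 0.0125, the next with 0.05/3 = 0.0167, then 0.05/2 = 0.025, then 0.05, stopping at the first failure.

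- The first threshold equals the Bonferroni one and the others are larger, so Holm rejects everything that Bonferroni rejects.
- With k true nulls, the first of them to be reached is tested at no more than 0.05/k, so the family-wise error is at most 5%.

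Average power per effective programme was obtained by simulation: four z-statistics with mean 3.126 for an effective programme and 0 otherwise, pairwise correlation 0.5, one million draws.

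| Programmes with d = 0.20 | One-tailed 0.0125 each (plan) | Holm, one-sided 0.05 | Holm, two-sided 0.05 |
|---|---|---|---|
| 1 | 0.81 | 0.81 | 0.74 |
| 2 | 0.81 | 0.83 | 0.76 |
| 3 | 0.81 | 0.86 | 0.78 |
| 4 | 0.81 | 0.89 | 0.82 |

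**4. If two-sided tests are intended.** At two-sided 0.0125 (critical value 2.498), power = Φ(3.126 − 2.498) = 0.735. Restoring 80% there needs 4,172 per arm, and 4,172 / 130 = 32.1, so 33 worksites instead of 28.

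**The case against.** The strongest defence is that nothing here is wrong. Bonferroni is valid, the level is stated, it is tied to the four planned contrasts, and the sample size follows from it. That stands. This point is an improvement and not the correction of an error. Bonferroni also has a practical advantage: its simultaneous confidence bounds follow directly, which Holm's do not.

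A reader might infer stronger things that the document does not support.

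- *That either the error rate or the 80% power must fail.* At the stated one-tailed 0.0125 both hold. Something fails only against a two-sided 5% family-wise standard, which the article never claims, and its hypothesis is directional.
- *That the family-wise error is about 15.6%.* This is the figure for four unadjusted two-sided tests at 0.05. No such test appears in the article, and it would contradict the one level given. That Statistical analysis does not repeat the level is detail which a condensed article may leave to the full analysis plan.
- *That one-tailed testing prevents harm from being seen.* Harm is collected on its own subscale of the implementation questionnaire and reviewed by the monitoring committee. Neither depends on the tail of the K6 test.
- *That changing to two-sided Holm would be free.* Like for like, Holm falls from 0.89 one-sided to 0.82 two-sided when all four programmes work, and with one to three working, two-sided Holm is below the plan's 0.81.

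**Conclusion.** The planned level is valid and meets the plan's own targets. Plain Bonferroni nevertheless gives up 8 percentage points of average per-contrast power (0.89 against 0.81) in the scenario that the plan itself assumes. The loss is 5 points if three programmes work, 2 if two do, and none if only one does.

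These figures rest on the article's own sizing method: intraclass correlation 0.05, equal clusters of 130, no attrition and large-sample tests. With 2 × 28 − 2 = 54 cluster degrees of freedom, single-contrast power would be about 0.79 at one-tailed 0.0125 and 0.70 at two-sided 0.0125. Holm's error control and its never rejecting less than Bonferroni do not depend on any of these assumptions, provided that the individual p-values are valid.

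The 80% power statement holds for one-tailed tests only.

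**What to change.** In Statistical analysis, state that the four 6-month intervention-versus-control contrasts on K6 are tested one-tailed with Holm's procedure at a family-wise 0.05. Step-down Dunnett is an alternative that uses the correlation from the shared control. Holm needs no assumption about that correlation.

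The sample size can stay as it is, since 0.81 remains the power when only one programme works. The cost is a sentence or two before the data are seen, and no extra worksites. The one-tailed 98.75% bounds can still be reported beside the Holm decisions, with a note that the two may occasionally disagree.

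If two-sided tests are intended, say so and restate the power. It is about 0.735 per contrast at two-sided 0.0125. With two-sided Holm it is about 0.74, 0.76, 0.78 and 0.82 when one, two, three or four programmes work.

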### Randomization

Each included worksite will be randomized to one of the five arms. The randomization will be stratified into 3 × 2 × 2 = 12 strata, based on worksite size (three strata, 5–49, 50–99, and 100–299 employees), industries (two strata, manufacturing/construction/transportation, and other industries), and the percentage of “high-stress” employees in the worksites (two strata, < 15% and ≥ 15%). Companies that engage in manufacturing/construction/transportation are considered qualitatively different from other companies because they exert a physical demand on the workers and focus on reducing work-related injuries. The cutoff point for the percentage of “high-stress” employees in the worksites was decided according to previous results of the National Stress Check Program in the potentially participating companies. Permuted block randomization (block size = 5) will be adopted for equal randomization. A stratified permuted block random table will be created by an independent biostatistician at the Department of Clinical Research, Kitasato University Hospital. This table will be managed by another research assistant in the Department of Public Health, Kitasato University School of Medicine, who will be blinded to researchers. The results of randomization will be open to the participating worksites and employees because the contents of all intervention programs will be notified before enrollment. The assessment of the outcomes will also be open because of the self-assessment of depression and anxiety. Data analysis will be blinded because it will be conducted by the second author (HH), who will not participate in the recruitment, enrollment, allocation, and delivery of the intervention programs.

### Statistical analysis

For the main analysis, repeated-measures multi-level mixed modeling will be used to test the effects of each intervention compared with the control at the 6-, 12-, and 18-month follow-ups. The interaction effect of the group (1 = intervention, 0 = control) by time will be considered an indicator of the intervention effect. The multi-level is based on employees (level 1) and worksites (level 2). The variables used in the stratified randomization (i.e., worksite size, industries, and the percentage of “high-stress” employees in the worksites) will be used as covariates. Intention-to-treat analysis will be adopted by including all employees who completed the baseline survey in the analysis. Multiple imputations will be conducted for missing values owing to dropouts. Effect sizes will be calculated as the standardized mean differences (d) of the scores on the K6 scale, based on the estimated mean differences.

The primary endpoint of the primary outcomes is set at the 6-month follow-up, and the corresponding statistical significance will be the primary indicator of effectiveness. If recruitment does not achieve the target sample size (140 worksites and 18,200 employees in total), we will assess the intervention effectiveness based on a minimally important difference. As the estimated effect size of the interventions is 0.20, the distribution-based approach [67] is useful for estimating the minimally important difference of depression and anxiety measured by the K6 scale. In a previous RCT among nonclinical workers in Japan [63], the standard deviation of the change in the K6 score at the 6-month follow-up was 4.16. From the distribution, 20% of the standard deviation is estimated to be 0.832. Therefore, a 0.85 score change in the K6 score at the 6-month follow-up is considered to be the minimally important difference.

The secondary and continuous outcomes will be analyzed using the same method as the primary outcomes, that is, multi-level mixed modeling. At the 12-month follow-up, the prevalence rate of worksite turnover in each intervention group will be compared with that in the control group using the logistic regression model. The means of the completion rates of the programs and the scores of implementation outcomes will be compared among the five arms using analysis of covariance. Per protocol set analyses will be conducted assuming that some participants may not complete all protocols of the intervention programs. All statistical analyses will be conducted using STATA version 17 (StataCorp LLC, Texas, USA).

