### Trial design

Regarding design, this will be an open, five-arm, parallel-group cRCT study. Of the five arms, four arms will offer intervention programs, and the other will be allocated as an active control group. Randomization will be conducted at the cluster (worksite) level. A worksite is defined as a place where related and systematic work can be conducted in the same place. After completion of the baseline survey, each worksite will be randomly assigned to one of the five arms at a 1:1:1:1:1 ratio. Randomization will be stratified by worksite size, industry, and the percentage of “high-stress” employees in the worksites. Data will be collected at both the worksite and employee levels, and the efficacy of the intervention programs will be evaluated at the employee level, considering the cluster (worksite) level effects. The study protocol has been registered with the University Hospital Medical Information Network (also known as UMIN) Clinical Trials Registry (UMIN-CTR, ID = UMIN000050949). This protocol has been reported in accordance with the SPIRIT guidelines [28].

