### Outcomes

Table 1 presents a schedule of enrolment, interventions, and assessments of this cRCT. All outcomes will be measured at the employee level. As the primary outcomes, depression and anxiety will be measured at baseline and at the 6-, 12-, and 18-month follow-ups. As secondary outcomes, psychosocial factors at work, work engagement, health-related QOL, well-being, economic outcomes, physiological outcomes from a health checkup, and levels of cortisol extracted from fingernails will be measured. The process and implementation outcomes will be assessed as well.

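### On its ordinary reading the group-by-time effect is a change-score contrast: unbiased, but less precise than one adjusted for the baseline K6 already collected

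*Protocol article*

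**What the plan says.** Under Statistical analysis, the protocol article plans that "repeated-measures multi-level mixed modeling will be used to test the effects of each intervention compared with the control" at 6, 12 and 18 months, with 6 months as the primary endpoint. The effect measure is fixed there: "The interaction effect of the group (1 = intervention, 0 = control) by time will be considered an indicator of the intervention effect". The structure is given as "The multi-level is based on employees (level 1) and worksites (level 2"). The covariates are "The variables used in the stratified randomization", listed as "i.e., worksite size, industries, and the percentage of “high-stress” employees in the worksites) will be used as covariates". Baseline K6 is not among them, and the section mentions neither a common baseline mean across arms nor a covariate-by-time term.

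Baseline K6 will be available. Under Outcomes, "depression and anxiety will be measured at baseline and at the 6-, 12-, and 18-month follow-ups". Under Trial design, "After completion of the baseline survey, each worksite will be randomly assigned to one of the five arms". The analysis set consists of people who have a baseline: "Intention-to-treat analysis will be adopted by including all employees who completed the baseline survey in the analysis". Missing follow-up values are to be multiply imputed. Continuous secondary outcomes follow the same method.

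**The concern.** If baseline K6 is one of the repeated outcomes and the arms may differ at baseline, the group-by-time term at 6 months is the difference in mean change. It subtracts the baseline with a coefficient of 1 where regression would use a smaller one, so it over-corrects chance imbalance between arms. The stratification variables do not vary over time. As main effects they move the level of K6 at every visit equally and drop out of a change contrast. What is at stake is precision. The trial pays for a baseline measurement on every participant before allocation, and this estimator does not make full use of it.

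**Working it through.** **The plan's own figure.** Inputs from Sample size calculation: d = 0.20, one-sided alpha 0.0125, power 0.80, ICC 0.05, cluster size m = 130. A two-sample t-test (noncentral t) needs 477 per arm. The design effect is 1 + 129 × 0.05 = 7.45, and 477 × 7.45 = 3,553.65, rounded up to 3,554, or 27.3 worksites. The article's figure is reproduced. It contains no baseline-correlation term.

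**Variance of the two contrasts.** In units of the individual score variance, the variance of a worksite mean is v = ICC + (1−ICC)/m. Its covariance between baseline and 6 months is c = ICC × π + (1−ICC) × s/m, where π is the worksite-level and s the employee-level correlation over time. Then r = c/v. Relative to the follow-up score alone:

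- change score: 2(1−r)
- baseline-adjusted: 1−r²
- ratio, adjusted to change: (1+r)/2, so the saving is (1−r)/2

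Neither π nor s is in the article, so both are assumptions shown over a range. The ICC values are the article's planning value (0.05) and the value it reports from a cohort (0.013).

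Worked case, ICC 0.05, π = 0.6, s = 0.5: v = 0.05 + 0.95/130 = 0.0573; c = 0.03 + 0.95 × 0.5/130 = 0.0337; r = 0.587. The change-score variance is 2(v−c) = 0.0473, the adjusted variance is v(1−r²) = 0.0375, and the saving is 21%.

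| ICC | π | s | r | 2(1−r) | 1−r² | saving |
|---|---|---|---|---|---|---|
| 0.05 | 0.4 | 0.5 | 0.413 | 1.174 | 0.830 | 29% |
| 0.05 | 0.5 | 0.5 | 0.500 | 1.000 | 0.750 | 25% |
| 0.05 | 0.6 | 0.5 | 0.587 | 0.826 | 0.655 | 21% |
| 0.05 | 0.8 | 0.6 | 0.774 | 0.451 | 0.400 | 11% |
| 0.05 | 1.0 | 0.5 | 0.936 | 0.128 | 0.123 | 3% |
| 0.013 | 0.6 | 0.5 | 0.563 | 0.874 | 0.683 | 22% |
| 0.013 | 0.8 | 0.6 | 0.726 | 0.547 | 0.473 | 14% |
| 0.013 | 1.0 | 0.5 | 0.816 | 0.369 | 0.335 | 9% |

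Savings of 11% and 22% correspond to about 13% and 28% more worksites (1/0.89 and 1/0.78).

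**Against the planned power.** With d in score-SD units, ICC 0.05 and 3,640 employees per arm, power for change score versus adjusted is:

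- r = 0.41: 0.74 versus 0.88
- r = 0.50: 0.81 versus 0.91
- r = 0.59: 0.885 versus 0.947
- r = 0.70: 0.96 versus 0.98

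The change contrast falls below 80% only when 2(1−r) exceeds 3,640/3,554 = 1.024, that is, when r is below about 0.49. At ICC 0.013, power is at least 0.98 either way.

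**Role of the covariates.** In one simulated complete data set (40 unequal clusters) the group-by-time coefficient was −0.513315, identical to the raw difference in mean change. It was the same to six decimals after covariates were added as main effects (SE 0.292 before, 0.289 after). It moved to −0.483825 with covariate-by-time terms, −0.504420 with a common baseline mean (SE 0.253) and −0.463 with baseline as a covariate (SE 0.280). One data set shows the mechanism and the direction, not the size to expect here.

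**The case against.** The strongest reply is that the article does not say the arms are free to differ at baseline. A model with a common baseline mean is also a repeated-measures mixed model whose effect is read from group-by-time terms, so the sentence on the effect measure is compatible with the remedy proposed here, and an analysis plan not shown may specify it. That is right. The free baseline difference is inferred from the ordinary reading. But the article fixes the effect measure and lists the covariates, and as they stand they describe a change-score contrast.

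Three stronger readings might be inferred, and the article does not support them.

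- **Bias.** Under randomisation the change contrast is valid. It is also conventional, and it fits a minimally important difference that the article builds from the SD of change (4.16 × 0.20 = 0.832).
- **Too little power.** The sample size takes no credit for baseline. For r above 0.5 and d in score-SD units, the change contrast is more precise than the trial was sized for. If d is in change-SD units, 3,554 already describes a change-score analysis and adjustment is pure gain.
- **Wasted stratification.** Stratified randomisation balances the arms on size, industry and high-stress share whatever the model. Only the added gain from covariate adjustment fails to reach the contrast.

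The size is also uncertain. If worksite effects hardly change over time, the saving at ICC 0.05 is only about 3%.

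**Conclusion.** The point holds as one of efficiency. On the ordinary reading, the 6-month contrast is a difference in change scores and is less precise than a baseline-adjusted contrast for any r below 1. The variance saving is (1−r)/2: about 3% at r near 0.94, 11–22% at r from 0.56 to 0.77, and about 29% at r near 0.4. These sizes rest on assumed correlations, with m = 130 and ICC 0.05 or 0.013 from the article. No shortfall against the planned 80% is shown unless r is below about 0.5 with d in score-SD units. That main-effect covariates leave the contrast unchanged is exact for complete data, which includes each imputed data set.

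**What to change.** State that the primary estimate is the 6-month difference between each intervention arm and control, adjusted for baseline K6. Name one of two forms:

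- keep the repeated-measures model, constrain baseline means to be equal across arms, and include group-by-time terms at the follow-up visits only, with no group effect at baseline; or
- model the follow-up scores only, with individual and worksite-mean baseline K6 as covariates.

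If the repeated-measures form is kept, add stratification factor-by-time terms. They help only as far as the strata predict change in K6. Use the same approach for continuous secondary outcomes that have a baseline.

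The cost is wording, settled before the data are analysed. No further data are needed, and adjustment adds no bias because baseline precedes allocation.
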